**Assessment of Response**

Pain scores and narcotic scores will be determined using the guidelines in following table:

PAIN AND NARCOTIC CATEGORIES AND SCORES

PAIN ANALGESIA

Severity 0 ‑ No pain 0 ‑ None

I ‑ Mild I ‑ Analgesics (ASA, *Bufferin, Tylenol, Anacin, etc.)*

2 ‑ Moderate 2 ‑ Mild Narcotic, (< 112 gr. *codeine, Darvon, etc.)*

3 ‑ Severe 3 ‑ Moderate Narcotic (> 112 < gr. *codeine, Percoan, etc)*

4 ‑ Strong 4 ‑Narcotic, (> 1 gr. *codeine, demerol, morphine, etc)*

Frequency 0 ‑ None 0 ‑ None

I ‑ Occasional (< *daily)* I ‑ p.r.n. (< *daily)*

2 ‑ Intermittent *(at least daily)* 2 ‑ q.d. (I *tab. or cap./day)*

3 ‑ Frequent (>. I < 3 *daily)* 3 ‑ b.i.d. t.i.d. (> I < 4 *tab. or cap./day)*

4 ‑ Constant *(most of the time)* 4 ‑ > t.i.d. (> 4 *tab. or cap./day)*

Pain Score = Pain Severity Grade x Pain Frequency Grade

**Narcotic Score** = Analgesia Severity Grade x Analgesic Frequency Grade

Response will be evaluated by questionnaires at follow‑up visit at 2, 4 and 8 weeks after completion of radiotherapy and by phone call interviews (when necessary for completeness) in poor compliance patients.

The "worst pain score" will be used as response endpoint. The time to maximal pain relief is the time from the first day of irradiation to the time of the lowest pain score for average pain.

Response Definitions

**Complete response** is defined as an average pain score of 0 for two consecutive analysis periods. Narcotic consumption must not be increased. **Partial response**. A decrease of at least 2 points in the worst pain score for two consecutive analysis periods. Narcotic consumption must not be increased. **No response** (any of the following): A pain score that does not change within 8 weeks from the start of radiation therapy.

A 2 point increase in worst pain score that is sustained at a higher level in the month following the first day of radiation therapy.

A pain score that drops by at least 2 points and subsequent sustained rise *(on 2 successive questionnaires)* of pain score by at least 2 points. Any patient with progressive pain in the treated area should have plain radiographs of the area to assess for bone stability and pathologic fracture.

References.

1.

Hoskin PJ. Scientific and clinical aspects of radiotherapy in the relief of bone pain. Cancer Surv. 7:69, 1988.

2. Tong D, Gillick L, Hendrickson FR. The palliation of symptomatic osseous metastases: the

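### The protocol declares worst pain the response endpoint but defines complete response on average pain, and ties neither score to a scale

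*Protocol*

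**What the plan says.** The statements below are all in the Protocol, under Assessment of Response and its Response Definitions.

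- The worst pain score "will be used as response endpoint".
- Time to maximal pain relief runs from the first day of irradiation "to the time of the lowest pain score for average pain".
- Complete response is "defined as an average pain score of 0 for two consecutive analysis periods", with no increase in narcotic use.
- Partial response is "A decrease of at least 2 points in the worst pain score for two consecutive analysis periods", with the same narcotic condition.
- No response includes "A pain score that does not change within 8 weeks from the start of radiation therapy", which names neither worst nor average pain, and "A 2 point increase in worst pain score that is sustained at a higher level" in the month after radiotherapy begins. A third criterion, a fall followed by a sustained rise, also refers only to a pain score.

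The section gives one pain formula, a severity grade (0 to 4) multiplied by a frequency grade (0 to 4), and no separate worst or average version of it. Pretreatment Evaluation names a different tool, the BPI. Under Objectives, the hypothesis concerns the rate of complete pain relief, and the primary objective is how often pain is relieved and for how long.

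**The concern.** Complete response is the only response category that names a score other than the declared endpoint. It is also the category that the hypothesis is about. The Background relies on a pooled analysis that chose complete response because investigators were thought likely to assess it consistently. Here two analysts could classify the same patient differently, each citing a sentence of the protocol.

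Two results are at stake: the complete response rate, and the overall response rate obtained by adding complete and partial responders. If the categories rest on different scores, they need be neither ordered nor mutually exclusive.

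**Working it through.** There is no stated figure to reproduce, and the point depends on no sample size or error rate. The check sets the definitions side by side and then follows them through.

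**Score named by each definition**

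| Item | Score named |
|---|---|
| Declared response endpoint | worst |
| Complete response | average |
| Partial response | worst |
| No response: no change | not specified |
| No response: sustained increase | worst |
| No response: fall, then rise | not specified |
| Time to maximal relief | average |

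**Reading 1: average and worst pain are two separate ratings.** Call them A and W, with 0 ≤ A ≤ W.

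1. W = 0 forces A = 0, but A = 0 does not force W = 0. Every complete responder on worst pain is therefore one on average pain, and not the reverse. Hence the rate based on average is at least the rate based on worst.
2. Let d be the share of average-based complete responders whose worst pain is not 0 on the two assessments. Then rate(worst) = rate(average) × (1 − d). The protocol gives neither rate(average) nor d, so only the direction is known.
3. Take a patient with A = 0 and W above 0 on two consecutive assessments and no narcotic increase:
   - if W fell by 1 point, the patient is a complete responder but not a partial responder, because the fall is under 2 points;
   - if W did not change, the patient is a complete responder and, reading the unspecified score as worst pain, also a non-responder.

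**Reading 2: average is the arithmetic mean of non-negative scores over a period.** A mean of 0 then forces every score to 0, so worst pain is 0 too. The two definitions of complete response coincide and nothing is inflated.

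**Which scale.** On the product score the range is 0 × 0 = 0 to 4 × 4 = 16, and any pain at any frequency scores at least 1 × 1 = 1. A product score of 0 therefore means no pain. The protocol does not say that the worst or the average score is this product, nor that either is a BPI rating. The 2-point threshold for partial response is therefore also without a stated scale.

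**Does replacing average by worst settle everything?** No. A patient whose worst pain goes from 1 to 0 reaches complete response with a fall of 1 point and still misses the 2-point partial criterion. That gap comes from the threshold at low baselines. It needs a rule on the order in which categories are assigned.

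**The case against.** The strongest reply is that the consequence depends on a reading the protocol never states. With one product formula, 0 means no pain, and a mean of 0 means no pain throughout. A complete responder who still hurts exists only if average pain is rated as its own item. This stands as a limit on the consequence. The protocol's separate wording for worst and average, together with its naming of the BPI at baseline, makes separate ratings plausible, but that is inference. The conflict in the wording remains under either reading.

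A reader might infer more, and three such inferences are not supported:

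- *A patient could enter with average pain 0 and be a complete responder without improving.* No minimum score is set at entry, but Eligibility Criteria require pain related to the metastasis, and the scoring table gives any pain at least 1. Intermittent pain has frequency grade 2, so with severity 1 or more it scores at least 2. The example fits poorly with the protocol's own table.
- *Using average pain for time to maximal relief breaches the endpoint sentence.* It does not. That time is a separate descriptive measure and is not a response category. At most it is on a different score and should be labelled so.
- *The inflation can be put in numbers.* If 40% were complete responders on average pain and 10% to 30% of them still had worst pain above 0, the rate on worst pain would be 0.40 × 0.90 = 36% down to 0.40 × 0.70 = 28%. Both inputs are invented, so the range is not evidence of size.

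It may also be said that this is a pilot gathering preliminary efficacy data, with no control arm or formal decision threshold stated. That lowers the consequence, but the definition still produces the result of the primary objective. Nor can the matter be left to an analysis plan: the protocol fixes two statements that disagree, and a plan that followed either would depart from the other.

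**Conclusion.** The contradiction is real and should be corrected before any patient's response is classified. Worst pain is the declared response endpoint, complete response is defined on average pain, and no scale is named for either.

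The effect on the complete response rate is conditional. If the two scores are separate ratings, the rate can only equal or exceed the rate on the declared endpoint, and a patient may fall into more than one category or into complete but not partial response. If average is a mean of non-negative scores, complete response is the same either way and the fault is one of wording. The document does not settle which applies and gives no figure for the size of the effect. It does not support a flat statement that the rate is inflated or that complete responders will still have pain.

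**What to change.** 1. Define complete response as a worst pain score of 0 on two consecutive assessments, with baseline worst pain above 0 and no increase in narcotic use.
2. Name the one instrument and scale that supplies the worst pain score (a BPI rating or the 0 to 16 product). Use it for complete response, partial response and every no-response criterion, including the two that now say only pain score.
3. Make the categories hierarchical: assign complete response first, then partial response, then no response. A low-baseline patient who reaches 0 is then counted once, as a responder.
4. Report average pain, including time to lowest average pain, as a separately labelled secondary measure.

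The cost is a few sentences of text, with no added visits or patients. It is more than a one-word swap, because the scale has to be chosen and the order of categories stated. The complete response rate may come out somewhat lower; by how much cannot be derived from the document.

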**OBJECTIVES**

Hypothesis: Given the hypothesis that regimens employing greater intensity radiation yield higher rates of pain relief, radiosensitization using a tumor targeted drug like Xeloda should improve the rate of complete pain relief as compared to radiosensitization with 5FU alone.

Primary Objective:

To determine the frequency and duration of pain relief and narcotic relief for the proposed regimen.

Secondary Objective:

To determine the toxicity of concurrent Capecitabine and radiotherapy in breast cancer patients with bone metastases.

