**Radiation Dose**

All patients will receive radiotherapy to a dose 30 Gy in 10fractions (3 Gy per fraction) over two weeks.

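### No response is not the complement of complete and partial response and overlaps partial response, so some patients fit no category and others fit two

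*Protocol*

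**What the plan says.** The primary objective (Objectives) is "To determine the frequency and duration of pain relief and narcotic relief for the proposed regimen". The Assessment of Response section supplies the classification.

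- **Score.** "Pain Score = Pain Severity Grade x Pain Frequency Grade", with each grade running from 0 to 4.
- **Complete response (CR).** Average pain of zero at two assessments in a row, with no rise in narcotic use.
- **Partial response (PR).** Worst pain down by 2 or more at two assessments in a row, with no rise in narcotic use.
- **No response.** Any one of three patterns:
  1. "A pain score that does not change within 8 weeks from the start of radiation therapy";
  2. a 2-point rise in worst pain that is "sustained at a higher level in the month following the first day of radiation therapy";
  3. "A pain score that drops by at least 2 points and subsequent sustained rise", where the rise is 2 points or more and is seen on two questionnaires running.

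Nothing assigns the remaining patients, and nothing says which category wins when two apply. Narcotic use is a condition for CR and PR but is not mentioned under No response.

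Questionnaires are due at the follow-up "visit at 2, 4 and 8 weeks after completion of radiotherapy". The Radiation Dose section fixes the gap between the two time origins: "All patients will receive radiotherapy to a dose 30 Gy in 10fractions (3 Gy per fraction) over two weeks".

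**The concern.** A response classification that feeds a primary frequency should put each patient in exactly one category. This one appears to fail both ways. Patients who match none of the definitions must be placed by someone's judgement after the data are seen. Patients who match both PR and pattern 3 can be counted as responders or non-responders with equal support from the text, which moves the numerator of the primary result. Patterns 1 and 2 also use windows counted from a different origin than the visits that would supply the data.

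These definitions are fixed in the protocol itself. The contradiction is therefore in the stated text and is not a detail left for an analysis plan.

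**Working it through.** The protocol gives no response rate or sample size to reproduce, so the check is of the rules' logic.

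**Inputs and readings**
- Attainable scores (product of two grades from 0 to 4): 0, 1, 2, 3, 4, 6, 8, 9, 12, 16, which is 10 values.
- A path is a baseline b > 0 followed by visit scores v1, v2, v3. Number of paths: 9 × 10³ = 9,000.
- Assumed readings: one score stands for both average and worst pain; changes are from the pretreatment score; pattern 1 is judged at the two visits inside 8 weeks from start; pattern 2 is read generously as a rise of 2 or more at visits 1 and 2; the rise in pattern 3 is measured from the low.

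**Visit times on the start-of-radiotherapy clock**

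2 + 2 = 4, 2 + 4 = 6 and 2 + 8 = 10 weeks. Week 8 from start is 6 weeks after completion, where no visit is scheduled. Only the week-4 visit lies in the first month.

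**Gaps: paths that meet no definition**

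| Path | Why nothing applies |
|---|---|
| 9 to 8, 8, 8 | The score changed, but by only 1 point |
| 9 to 9, 4, 9 | Fall of 2 or more at visit 2 only |
| 6 to 6, 8, 8 | Rise begins after the first month |
| 6 to 0, 0, 0, narcotics increased | Fails the narcotic condition for CR and PR; matches no No response pattern |

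**Overlap**

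Pattern 3 needs v1 ≤ b − 2, v2 ≥ v1 + 2 and v3 ≥ v1 + 2. PR needs two consecutive visits at b − 2 or lower. Both hold exactly when v1 + 2 ≤ v2 ≤ b − 2 and v3 ≥ v1 + 2.
- 12 to 6, 8, 8: 8 ≤ 8 ≤ 10, and v3 = 8 ≥ 8. Both apply.
- 16 to 4, 6, 6: 6 ≤ 6 ≤ 14, and v3 = 6 ≥ 6. Both apply.

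**Count of paths, narcotics not increased**
- CR or PR: 3,305. No response: 3,092. Both: 531.
- Classified: 3,305 + 3,092 − 531 = 5,866. Unclassified: 9,000 − 5,866 = 3,134.
- 3,134 / 9,000 = 34.8% unclassified; 531 / 9,000 = 5.9% in two categories.
- Effect of the overlap on the numerator, in paths: 3,305 / 9,000 = 36.7% if these count as responders, against (3,305 − 531) / 9,000 = 2,774 / 9,000 = 30.8% if they do not.

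**Sensitivity to the readings**

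| Reading | Unclassified | In two categories |
|---|---|---|
| As above | 3,134 / 9,000 = 34.8% | 531 = 5.9% |
| Pattern 1 judged at all three visits | 3,215 / 9,000 = 35.7% | 531 = 5.9% |
| No change read as less than 2 points | 2,816 / 9,000 = 31.3% | 543 = 6.0% |
| 0–10 scale (10 × 11³ = 13,310 paths) | 5,295 / 13,310 = 39.8% | 630 = 4.7% |
| Narcotics increased | 5,908 / 9,000 = 65.6% | 0 |

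**Do the clocks change the responder count?**

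Pattern 1 requires v1 = v2 = b. CR and PR each need two consecutive visits, and both possible pairs include visit 2. A patient unchanged at weeks 4 and 6 therefore cannot reach CR or PR at the scheduled visits, even with clear relief at week 10 (12 to 12, 12, 4). No path meets both pattern 1 and a response. The same holds for pattern 2 as read here. All 531 overlaps come from PR with pattern 3.

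**The case against.** The best defence is that CR and PR are defined in their own right. The rate (CR + PR) over all treated patients can be computed without using No response, and no text says that unclassified patients are dropped. This is correct. A reader might infer that the response frequency has no valid denominator, or that it is inflated by some known amount. The first does not follow. The second needs both a distribution of pain scores and an exclusion rule, and the protocol contains neither.

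A reader might likewise infer that many patients would go unclassified. The enumeration gives every path equal weight, which real patients will not follow, so it shows that the gaps exist but not how common they are.

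On timing, it is tempting to say that the 8-week window wrongly fixes late improvers as non-responders. It does not, because the two-assessment requirement already rules out a response for them. Nor is pattern 2 unusable on every reading: a rise seen at week 4 and still present at week 6 could be accepted as sustained, although the text does not say so.

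On duration, one might argue that pattern 3 removes the relapses that the duration objective needs. With three visits it requires the low at visit 1 and the rise at visits 2 and 3. A responder steady at visits 1 and 2 who relapses at visit 3 (12 to 4, 4, 12) is PR only. The effect on duration is confined to the overlap cases.

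Finally, this is a pilot collecting preliminary efficacy data, with no stated success threshold. That limits the consequence of a misclassified patient but does not settle where that patient belongs. The gaps and the overlap survive every point above. The overlap would vanish only if the rise in pattern 3 were measured from baseline, which the wording does not suggest.

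**Conclusion.** Wrong as written. Two defects are certain from the text: the three categories are not exhaustive, and PR and pattern 3 of No response can both apply to one patient with no rule to decide. The second directly affects who counts as a responder for the primary objective.

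The size, about 35% of possible paths unclassified and about 6% doubly classified, describes the rules and not the trial population. It rests on the product scale, on narcotics not being increased, and on the readings listed above. Across the alternative readings with narcotics not increased, the unclassified share stays between 31.3% and 39.8%.

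The mismatch of time origins is real but lesser: a wording fault that does not by itself alter the count of complete and partial responses.

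**What to change.** Amend the response definitions before any patient's response is classified:

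1. Define No response as every treated patient who meets neither CR nor PR. This takes in unconfirmed falls, 1-point changes, late worsening and relief with increased narcotics.
2. State the precedence: complete, then partial, then no response.
3. Treat a sustained rise after a confirmed response as the end of that response for the duration analysis, not as No response. Say how the end is dated, because in every overlap path visit 2 both confirms the response and begins the rise.
4. Express the windows in scheduled visits with one stated time origin, in place of 8 weeks and one month from the first day.
5. Report (CR + PR) over all treated patients.

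Under items 1 and 2, every path falls in exactly one category by construction. The cost is wording only, with no new visits or data. The reported rate may be less favourable than one computed among classified patients only.

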**APPENDIX 11**

**KARNOFSKY PERFORMANCE SCALE**

100 Normal; no complaints; no evidence of disease

90 Able to carry on normal activity; minor signs or symptoms of disease

80 Normal activity with effort; some sign or symptoms of disease

70 Cares for self; unable to carry on normal activity or do active work

60 Requires occasional assistance, but is able to care for most personal needs

50 Requires considerable.assistance and frequent medical care

40 Disabled; requires special care and assistance

30 Severely disabled; hospitalization is indicated, although death not imminent

20 Very sick; hospitalization necessary; active support treatment is necessary

10 Moribund; fatal processes progressing rapidly

0 Dead
